#### Rare (< 0.1%) side effects:

Gastrointestinal: pancreatitis

Genitourinary: proteinuria

Hematologic: low red cell count, pancytopenia, thrombocytopenia

Musculoskeletal: bone pain

Ocular: ocular maculopathy

Frequency not reported:

Hematologic: granulocytopenia, agranulocytosis

Hepatic: hepatotoxicity, hepatic abnormalities\*, jaundice\*, hepatocellular damage\*

\*severe hepatic adverse events reported during prolonged higher dose treatment

Ocular: retinal damage

Postmarketing reports:

Dermatologic: erythema multiforme, Stevens-Johnson syndrome, reversible alopecia (thinning of hair and moderate hair loss)

Gastrointestinal: diarrhea

Hematologic: aplastic anemia, bone marrow suppression (mainly in patients with liver disease), neutropenia, agranulocytosis, pancytopenia

Hepatic: acute liver failure, elevated liver enzymes and hepatitis

Musculoskeletal: rhabdomyolysis

Nervous system: somnolence, convulsion, headache

Ocular: blurred vision

Renal: acute renal failure

Other: asthenia, fever

**9.3.5 Adverse events**Documenting, Recording and Reporting Adverse Events

At each contact with the subject, information regarding adverse events will be elicited by appropriate questioning and examinations and will be:

- immediately documented in the subject's medical record/source document
- The study clinicians/physicians will visit the participants in their villages every day during the treatment period to closely supervise possible (severe) adverse events. Additionally the phone numbers of the trial clinicians will be handed to the village health workers as well as to the participants. In case of an emergency between the visits, the clinicians have to be called and will come to the participants whenever needed. In case the participant has to go to a hospital for further examinations and treatment, the transport and medical care will be paid by the research team. An insurance for participants and the medical personal involved in the project and directly in charge of the patients will be provided.

**9.4 Assessment of immunological parameters**

Plasma will be aliquoted (2x2ml) in cryotubes, immediately frozen and stored for determination of the immunological parameters. Whole blood cells will be stained for distinct immune populations and measured by flow cytometry. Whole blood cells will also be used directly in cell culture assays to determine intracellular cytokine profiles upon stimulation. A fraction of whole blood cells will be stored at -80°C to repeat the assays or verify another parameter which is requested by reviewers during publication.

**9.5 Source documentation**

Complete source documentation (e.g. laboratory test reports, medical records) will be required for each participant for the entire duration of the study. Case Report Forms (Annex CRF) will be used to record data for subjects enrolled in the study. The investigator is responsible for the accuracy and completeness of the data reported to the study sponsor. Data reported in the CRFs derived from source documents should be consistent with them or the discrepancies should be explained.

## 9.6 Study documentation, data safety and confidentiality

Pseudonymity of the study participants will be maintained by assigning study participants a unique study identification number. All data, blood samples and laboratory results will be recorded and analyzed with this unique identification number and no personal identifiers. All information collected, including names, specific addresses, etc. that could identify participating subjects will be kept confidential and available only to the investigators and authorized study personnel.

All data will be double entered by trained personnel directly in Cameroon and subsequently cleaned by the Data Manager in Bonn using the data management program REDCap®. The data bases will be password protected and access to password will be authorized by the Principal Investigators. Electronic data files will be stored on operated and dedicated servers in the respective study laboratories. Analyses of the data will be performed on copies of the original data files ensuring raw data accessibility at all times. Regular backups to an external hard drive will be carried out ensuring protection against data loss. The anticipated funding body (DFG) hold an annual meeting to check the progress and status of each project.

## 9.7 Data Collection & Management

All necessary precautions are taken to ensure that our research data is stored, archived and disposed of in a safe and secure manner during and after the conclusion of the research project. Laboratory notes are reported daily in the researcher's personal laboratory book. These books are the property of the Institute and remain there even after the departure of the scientist. Regular electronic backups are made of the raw data from computers attached to institute equipment such as the flow cytometer. Data for publications are collected and stored on the Institute's server which is protected from external tampering by the usual precautions.

The investigator has ultimate responsibility for the accuracy, authenticity, timely collection and reporting of all clinical, safety, laboratory data entered on the Case Report Forms (CRFs). Data will be captured using paper CRF specially designed for the study and approved by the IRBs. The CRFs must be signed by the investigator or by an authorized staff member to attest that the data contained on the CRFs is true. Any corrections to entries made in the CRFs, source documents must be dated, signed and explained (if necessary) and should not obscure the original entry. All paper CRFs will be secured in fireproof locking cabinet. All study personnel participating will undergo training in the procedures to be used in the study.

Research data collected on paper CRFs will be transcribed and entered onto the REDCap (Research Electronic Data Capture: <http://project-redcap.org/>) system using double data entry. The EDC application is a secure encrypted web application for building and managing online surveys and databases specifically geared to support data capture for research studies. REDCap meets regulatory requirements for GCP/GCLP, 21 CFR Part 21 and HIPAA compliant with full audit trails capability for tracking data manipulation and user activity, as well as automated export procedures for seamless data downloads to Excel, PDF, and common statistical packages (SPSS, SAS, Stata, R). The equipment for data transfer may include laptops, or mobile applications for tablet computers and/or smartphones with either Android or iOS operating systems. All electronic tools will be password protected.

Study data will be managed using REDCap electronic data capture tools hosted at the University Hospital Bonn. REDCap (Research Electronic Data Capture) is a secure, web-based application designed to support data capture for research studies, providing: 1) an intuitive interface for data entry; 2) audit trails for tracking

data manipulation and export procedures; 3) automated export procedures for seamless data downloads to common statistical packages; and 4) procedures for importing data from external sources. Details on data management (procedures, responsibilities, data corrections, if any, which may be made by Data Management staff themselves, etc.) will be described in a data management plan prior to the trial. During the trial, the performance of data management and any deviations from the data management plan will be documented in a data management report. Before any data entry is performed, the trial database will be validated and the technical specifications of the database will be documented in a variable plan. Processing of data is done via Double-Data-Entry. The two entries will then be compared with each other and verified. An audit trail will be created to provide an electronic record of which data were entered or subsequently changed, by whom and when. SAS software will be used to review the data for completeness, consistency and plausibility. The checks to be programmed will be specified beforehand in a data validation plan, as required by the subject protocol. After running the check programs, the resulting queries will be sent to the investigator for review of his/her data. Answered queries will also be entered twice, verified and the updated data will then be transferred to the database. All programs which can be used to influence the data or the data quality will be validated (e.g. check programs, programs used for the input of external data, etc.).

All data will be checked for consistency and plausibility by the monitor and by the data management. Inconsistencies will be queried and discussed with the investigator. After data clearance the data base will be locked and data will be used for statistical analysis.

## **9.8 Retention of records**

All written forms (i.e. consent and data collection forms) will be stored in the study laboratories in Cameroon and Bonn. All forms will be labelled and filed in lockable filing cabinets with the Study Protocol Name, Principal Investigators' names and collection dates. Keys will be kept with the principal investigators or the persons responsible for data management. Study-related documents will be maintained by the investigator for a period of 15 years following completion of study. The electronic database will be stored for 15 years by the Principal Investigators. All data will be readily available for review upon request by the national authorities and the IRBs.

## **9.9 Protocol revisions**

Revisions in the study protocol can only be performed following renewed permission from the local ethics authorities. This does not apply to changes made to reduce discomfort or avert risk to study participants.

## **9.10 Sample transport from Cameroon to Bonn**

Analysis from blood and urine samples will include the glycemic and biochemical analyses via the Reflotron system and multiplex ELISA measurements as well as multicolor flow cytometric analyses of intracellular cytokine producing T cells from blood samples will take place in Bonn, Germany. We do not intend to use the obtained material for commercial purposes. Therefore the project represents an ABS constellation (Tabelle in Punkt 3. DFG-Vordruck 1.021 – 5/08) that requires for export of biological material (blood and urine samples) to the German partner institute a simple ABS agreement (Tabelle in Punkt 3. DFG-Vordruck 1.021 – 5/08) and a standardized Material Transfer Agreement will be used ensuring and promoting technology transfer and long-term sharing of the benefits derived from those samples

## **9.11 Termination of the trial for individual subjects**

### *9.11.1 Termination by the participant*

A patient may decide to withdraw from the study at any time and for any reason. The Investigator should attempt to determine the reason for the subject's decision. There will be no disadvantage for the participant as a result of a withdrawal. If a participant does not return for a scheduled visit, every effort should be made to contact the participant. The investigator should inquire about the reason for withdrawal and the participant should be followed-up regarding any unresolved adverse events, if possible. In any circumstance, every effort should be made to document the participants' outcome. Therefore all participants, even if the participant was withdrawn from the trial treatment, will be encouraged to come for the follow-up visits.

### *9.11.2 Termination by the investigator*

The investigator may withdraw a patient for any of the following reasons:

- An individual subject's decision
- Any clinical adverse events, laboratory abnormality or other medical condition or situation such that continued participation in the study would not be in the best interest of the subject. Subjects will be followed for the duration of the study for indicated safety assessments.
- Non-compliance with study procedures to the extent that it is potentially harmful to the subject or to the integrity of the study data.
- A change in the subject's baseline condition after enrolment so that the subject no longer meets the inclusion/exclusion criteria.

In any circumstance, every effort should be made to document the participants' outcome. Therefore all participants, even if the participant was withdrawn from the trial treatment, will be encouraged to come for the follow-up visits.

## **9.12 Study Monitoring**

To ensure accurate, complete, consistent, and reliable data, and ensure the patients' safety, the investigator's site and trial procedures will be monitored by the ministry of public health, the Division of Operational Research in Health (DROSS). The public health's representative will visit the site:

- to evaluate the progress and recruitment of the trial,
- to review the source documents and CRFs for protocol compliance, accuracy and validation,
- to assess facilities and equipment,
- to check for protocol compliance,
- to assure the (severe) adverse events reporting,
- to verify proper handling and dispensing of the IMP(s), and other factors.

The investigator agrees to cooperate with the monitor to ensure that any problems detected in the course of these monitoring visits are addressed and resolved, and therefore ensures the accuracy and consistency of the trial with GCP and all applicable laws. The investigator allows the monitor to have access to all trial related original data and documents relevant for the monitoring of the trial.

## 10 STATISTICAL CONSIDERATIONS

### 10.1 Sample size justification and statistical analysis

This is a partially randomized controlled open label pilot trial to gain first experience on the impact of infections with the filarial nematodes *O. volvulus* and *M. perstans* on the metabolic profile and the systemic immune response in lean and obese patients. As there is limited data that exists to inform on study design, we will use 400 persons per group (*O. volvulus* infected, *M. perstans* infected, and endemic non-helminth-infected persons) with half of the participants of each group having a BMI of  $\geq 30$  and the other half of below 25. Thus, cases (those with active worm infections) and controls (worm infection free) will be included at a case: control ratio of 1:1:1. All *M. perstans* infected patients and all *O. volvulus* infected persons will further be treated in an interventional pilot study to test the changes in the metabolic profile and the systemic immune responses following treatment with doxycycline.

Our primary endpoint will be quantitative changes in insulin resistance (HOMA-IR). The logarithmic transformed HOMA-IR values will be compared between the three obese subgroups with a two-step test procedure. In the first step a one factorial analysis of variance will be used to test the hypotheses of equal mean log(HOMA-IR) values in the three groups at a level of 5%. In case that this hypothesis can be rejected the mean log(HOMA-IR) values will be checked for equality for each pair of groups with a two-sided t-test at a level of 5% for each test. This test procedure maintains a multiple level of 5%. From literature data (33) we expect the logarithm of the HOMA-IR to be normally distributed with a standard deviation of 0.83. With the planned sample size of 200 cases per group the intended test procedure then has a power of 80% to detect a deviation of 0.3 in the mean log(HOMA-IR) values between two of these groups. This is equivalent to reduction of 25% of the HOMA-IR in comparison between these two groups.

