### 6.3 Group allocation

Volunteers of both sexes (stratified according to age, gender and socio-economic status) with a BMI above  $\geq 30$  (obese) and  $< 25$  (lean), will be assigned to the following groups according to the clinical assessment (Fig. 1):

- 200 obese and 200 lean individuals with onchocerciasis (presence of microfilariae in the skin, *O. volvulus* PCR positive). All onchocerciasis patients will be treated with 200mg doxycycline daily for 6 weeks. They will also receive single dose of 400 mg albendazole every three months with a total of 4 treatments. *M. perstans*, *O. volvulus* as well as *Loa loa* co-infected individuals will be included and treated with doxycycline and albendazole, in case that not sufficient individuals with *O. volvulus* infection alone are identified.
- 200 obese and 200 lean individuals with *M. perstans* (presence of microfilariae in the blood, PCR positive). All *M. perstans* infected obese and lean patients will be randomly selected for anti-filarial therapy with 200mg of doxycycline daily for 6 weeks. They will also receive single dose of 400 mg albendazole every three months with a total of 4 treatments. *M. perstans* and *O. volvulus* as well as *Loa loa* co-infected individuals will be included and treated with doxycycline and albendazole, in case that not sufficient individuals with *M. perstans* infection alone are identified.
- 200 obese and 200 lean *Loa loa* infected and 200 obese and 200 lean healthy endemic individuals without onchocerciasis, *Mansonella perstans* infection with normal eosinophil counts and IgE levels. All endemic individuals will receive single dose of 400 mg albendazole every three months with a total of 4 treatments.

[figure not shown]

Fig. 1: Distribution of study participants

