### 9.3 Intervention pilot study

An intervention study analyzing the kinetic of changes in the metabolic and immunological profiles after anti-filarial treatment will be conducted. All patients of the *M. perstans* infected obese and lean subjects will receive anti-filarial therapy (Fig. 1). The known treatment option for *M. perstans* infections with 200mg of doxycycline daily for 6 weeks will be used (28, 29) since ivermectin is known not to deplete the *Mansonella* adult worms and to have only modest effect on microfilariae (30). This doxycycline therapy will permanently sterilize the female adult *Mansonella* worms and lead to the death of the adult worms over time. All onchocerciasis patients will also receive the anti-filarial therapy with 200mg of doxycycline daily for 6 weeks, which was previously shown to sterilize the female adult *Onchocerca* worms and lead to the death of the adult worms over time (31, 32). Patients co-infected with *Onchocerca* and *Mansonella* will also be treated with 200mg of doxycycline daily for 6 weeks. As *L. loa* does not contain *Wolbachia* endosymbionts, doxycycline treatment will not affect *L. loa* co-infection. Onchocerciasis patients, *M. perstans* infected patients, *L. loa* infected individuals and endemic controls will receive single dose of 400 mg albendazole every three months with a total of 4 treatments for the elimination of soil transmitted helminths. Treatment of *L. loa* infected individuals with albendazole does not kill the adult worms, but reduces the microfilariae load in a safe and well tolerated manner. Treatment of onchocerciasis patients with ivermectin as originally intended is not an option, as the study site selected for our study received more than 10 years of ivermectin MDA and suboptimal responses were observed with reoccurring microfilaridermia within less than one month. As a 6-week treatment with doxycycline is not ethically acceptable for endemic controls, those participants will only receive albendazole treatments. Although *Mansonella* infections do not cause pathology and there is no MDA program for mansonellosis we are now treating all *Mansonella* patients with doxycycline. The benefit of the *Mansonella* patients to receive doxycycline may be a lower risk to acquire co-infections such as tuberculosis and HIV. On the other hand we hypothesize that clearance of the *Mansonella* infection by doxycycline therapy may have a negative effect on insulin sensitivity in obese patients, but this needs scientific evidence and was not sufficient to convince the participants of the study not to be treated for the duration of this study. An overview of the groups and subject numbers is provided in Fig.1.

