#### Frequent (1-10%) side effects:

*Metabolic and Nutritional:* Increased blood lactate dehydrogenase (2%), increased blood glucose (1%)

*Respiratory:* Nasopharyngitis (5%), sore throat (5%), sinus congestion (5%), coughing (4%), sinus headache (up to 4%), sinusitis (3%), bronchitis (3%), nasal congestion (2%), pharyngolaryngeal pain (1%)

*Infections and Infestations:* infection (2%), fungal infection (2%), influenza (2%)

*Reproductive Disorders:* Menstrual cramp (4%), bacterial vaginitis (3.3%), vulvovaginal mycotic infection (2%)

*Hepatic and Biliary:* Increased aspartate aminotransferase (2%)

*Body as a whole – general:* Injury (5%), pain (up to 4%), back pain (up to 3%), back ache (2%)

*Dermatologic:* Rash (4%)

*Gastrointestinal:* Vomiting (8.1%), toothache (7%), tooth disorder (6%), dyspepsia (6%), diarrhea (up to 6%), periodontal abscess (4%), acid indigestion (4%), upper abdominal pain (2%), abdominal distention (1%), abdominal pain (1%), stomach discomfort (1%), dry mouth (1%)

*Musculoskeletal:* Joint pain (6%), muscle pain (1%)

*Cardiovascular:* Hypertension (3%), increased blood pressure (2%)

*Psychiatric:* Anxiety (2%)

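### Section 10.1 labels the primary endpoint a change in HOMA-IR but tests and sizes between-group values at no named visit, keeps randomisation wording for a trial that randomises nothing, and names no comparator for post-treatment change

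*Protocol*

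**What the plan says.** **Primary endpoint (10.1).** It is introduced as a change: "Our primary endpoint will be quantitative changes in insulin resistance (HOMA-IR". The next sentence describes something else: "The logarithmic transformed HOMA-IR values will be compared between the three obese subgroups with a two-step test procedure". The SD of 0.83 is given for log(HOMA-IR) itself, and the 0.3 is a difference between two group means. No visit, baseline or change score is mentioned. The primary objective (5.1) is association and the title page calls the study cross-sectional. What happens after treatment is the secondary objective (5.2).

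**Randomisation.** Section 10.1 opens: "This is a partially randomized controlled open label pilot trial". Section 6.3 says of all M. perstans patients: "infected obese and lean patients will be randomly selected for anti-filarial therapy". The synopsis, 9.3 and a later sentence of 10.1 treat every M. perstans and every O. volvulus patient. In the synopsis the randomised-controlled label is struck through.

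**Treatment question.** Section 10.1 plans, in the treated patients, "to test the changes in the metabolic profile and the systemic immune responses following treatment with doxycycline". It names no comparator for that change. Of the endemic controls, 9.3 says "those participants will only receive albendazole treatments"; Loa loa patients receive the same albendazole course. Section 9.3 follows all subjects at 12 and 18 months.

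**The concern.** A primary endpoint has to fix a variable and a time. Here the label says change and the test says value, and several choices stay open: the value at baseline, 12 or 18 months, or a change between them. The choice could be made after the data are seen.

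The randomisation wording states a design property that the trial does not have.

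The post-treatment question is the one with policy weight. Section 4.3 wants to learn whether mass treatment may facilitate type 2 diabetes, and 9.3 hypothesises that clearing M. perstans may worsen insulin sensitivity in obese patients. Without a concurrent comparator, ageing, weight change, assay drift or albendazole could produce the same signal.

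**Working it through.** **1. Does the sizing describe values or changes?** Inputs from 10.1: SD 0.83, difference 0.3, 200 per obese group, two-sided 5%.
- Standard error of a difference in means: 0.83 × √(2/200) = 0.083. Ratio: 0.3/0.083 = 3.61. Pairwise power: Φ(3.61 − 1.96) = 95.1%.
- Two-step procedure (ANOVA, then t-test), by simulation: about 90.5% with the third group midway, 93.8% if it equals one of the other two.
- The stated 80% is therefore not reproduced. It is conservative for a comparison of values, and that is a separate matter.
- exp(−0.3) = 0.741, a 26% lower HOMA-IR. This agrees with the stated 25%, which 10.1 describes as a comparison between two groups.

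Every input describes values at one time.

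**2. Can the same sizing serve a change endpoint?** SD of change = 0.83 × √(2(1 − ρ)), where ρ is the within-person correlation. The protocol gives no ρ, so a range is assumed.

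| ρ (assumed) | SD of change | Two-step power, difference 0.3, n = 200 |
|---|---|---|
| 0 | 1.17 | 60% |
| 0.3 | 0.98 | 78% |
| 0.5 | 0.83 | 90% |
| 0.7 | 0.64 | 99% |

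The SD of change equals 0.83 only at ρ = 0.5. For a change endpoint the stated power cannot be verified.

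**3. Is anything randomised?** Section 6.3 applies random selection to all M. perstans patients, which selects nobody. Neither infection has an untreated arm, and controls and Loa loa patients are defined by infection status. No randomised comparison is described anywhere.

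**4. What would a purely before-after test be exposed to?** This illustrates a reading that the protocol does not fix. Assume a paired test in 200 people at two-sided 5%, no true effect of clearance, and a drift common to everyone. SE = SD of change/√200, and the chance of declaring an effect is P(|Z + drift/SE| > 1.96).

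| ρ (assumed) | SE | Drift 0.05 (about 5%) | Drift 0.10 (about 11%) |
|---|---|---|---|
| 0.3 | 0.0694 | 0.05/0.0694 = 0.72 → 11% | 1.44 → 30% |
| 0.6 | 0.0525 | 0.95 → 16% | 1.91 → 48% |
| 0.7 | 0.0455 | 1.10 → 20% | 2.20 → 59% |

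A difference in change against a concurrent group removes any drift that both groups share.

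**The case against.** **The endpoint wording is loose, not wrong.** The sentences after it define the comparison, and the objective and title page make baseline the natural reading. This largely stands and shows which correction is right. It does not supply the missing visit.

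**The randomisation wording is leftover text.** The synopsis has struck the term and 9.3 explains why all M. perstans patients are now treated. That stands: the correction is editorial. A reader might infer that the results will be presented as randomised evidence, but the protocol does not say so.

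**The treatment analysis may be in the SAP, and controls are not excluded.** This is the strongest objection. A reader might infer that 10.1 commits to a within-group analysis and leaves the controls unused. It does not: no paired test is named and no comparator is ruled out. Sections 4.1 and 4.3 mention comparison with endemic controls alongside follow-up after treatment. A model for a secondary objective may properly sit in the SAP. What remains is that 10.1 describes the aim as change in the treated groups alone, while a concurrent group is already being followed.

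**The confounders can be overstated.** Section 9.3.1 lists raised blood glucose (1%) for doxycycline, from which a reader might infer a bias towards apparent harm. The same section also lists hypoglycaemia. Section 6.5 puts the first follow-up 12 months after treatment onset, about 46 weeks (52 − 6) after a 6-week course ends. No direction of bias is established. Season largely cancels at 12 months, though not necessarily at 18.

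**Conclusion.** Two faults are in the text as it stands. Section 10.1 names a change endpoint while testing and sizing values at no stated visit, and 6.3 and 10.1 claim a randomisation that does not exist. Neither conclusion rests on an assumption.

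The third part is weaker. The protocol names no comparator for post-treatment change, so naming one is a worthwhile improvement and not the correction of a stated error. The figures of 11% to 20% and 30% to 59% show what a before-after reading would risk. They depend on an assumed paired test, correlation and drift, and do not measure a planned analysis.

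Nor do the documents support a claim that the study is underpowered. For values at baseline the stated inputs give more than 80%; for change, power depends on a correlation that is not given.

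**What to change.** **Primary endpoint (10.1).** Define it as between-group differences in pre-treatment log(HOMA-IR), and name the visit that supplies it. Section 8.2 lists HOMA-IR at screening but venous fasting glucose at enrolment.

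**Randomisation.** Delete the two phrases quoted from 6.3 and 10.1.

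**Secondary objective.** Compare change in log(HOMA-IR) from baseline at 12 and 18 months in the doxycycline-treated groups with the concurrent change in the albendazole-only endemic controls, as a group-by-time contrast adjusted for baseline covariates. Use Loa loa patients only as a supportive comparator, because 9.3 says albendazole lowers their microfilariae. State that the contrast is non-randomised, is confounded with infection status, and cannot fully separate a drug effect from clearance.

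**Cost.** Wording in 6.3 and 10.1, a little more analysis, and a more modest causal conclusion. No new visits or samples are needed at the 12- and 18-month follow-ups in 6.5 and 9.3. The differing schedules in 6.2 (12-month intervals over 3 years), 6.4 (6-month intervals over 3 years) and 13.4 (six blood draws at 12-month intervals) must be reconciled with these.

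### The stated 80% power does not follow from the protocol's own inputs: 200 per obese group gives about 90% to 94%, and 80% needs only about 133 to 150

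*Protocol*

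**What the plan says.** Everything needed for the calculation is in one paragraph of Protocol section 10.1.

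- Comparison: "The logarithmic transformed HOMA-IR values will be compared between the three obese subgroups with a two-step test procedure".
- Step 1: "a one factorial analysis of variance will be used to test the hypotheses of equal mean log(HOMA-IR) values in the three groups at a level", namely 5%.
- Step 2, only if step 1 rejects: equality is tested "for each pair of groups with a two-sided t-test at a level of 5% for each test".
- Variability: "we expect the logarithm of the HOMA-IR to be normally distributed with a standard deviation of 0.83".
- Size: "With the planned sample size of 200 cases per group".
- Result claimed, for any two of the groups: "the intended test procedure then has a power of 80% to detect a deviation of 0.3 in the mean log(HOMA-IR) values". The section equates this with a 25% reduction in HOMA-IR.

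The paragraph gives no allowance for losses or unusable samples, no design effect, no adjustment beyond the two-step procedure, and no assumed position for the third group's mean.

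**The concern.** A standardised difference of 0.3/0.83 = 0.36 with 200 per group is well above what 80% power requires: a single two-sided t-test needs only about 121 per group. The ANOVA gate costs some power, but not enough to bring the figure down to 80%. So either the figure was miscalculated or an assumption behind it was left out.

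This is the only power calculation in the protocol, so it is what a reader will use to judge what the obese comparison can deliver. Recruitment is by village (section 8.1), blood is drawn after an overnight fast (section 9.2), and participants may withdraw at any time (section 9.11.1). Each of these can reduce the effective number below 200. With the power understated, nobody can tell whether such losses are already covered. Any recruitment shortfall would also look like a fall below 80% when it need not be one.

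**Working it through.** **Inputs, all from section 10.1.** SD 0.83, difference d = 0.3, n = 200 per group, three groups, ANOVA at 5%, then two-sided t-tests at 5% each. The log is natural: exp(-0.3) = 0.741, a reduction of 25.9%, which agrees with the stated 25% up to rounding.

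**1. Pairwise t-test alone.** Noncentrality = (d/SD) × √(n/2) = (0.3/0.83) × √100 = 3.61. Power is 95%.

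**2. ANOVA step alone.** Noncentrality λ = n × Σ(μᵢ − μ̄)²/SD², with SD² = 0.6889 and degrees of freedom 2 and 597.
- Third mean midway (0, 0.15, 0.30): Σ = 0.15² + 0 + 0.15² = 0.045, so λ = 200 × 0.045/0.6889 = 13.06 and power is 90.8%. This position makes λ smallest for a given d.
- Third mean equal to one of the pair (0, 0, 0.30): Σ = 0.1² + 0.1² + 0.2² = 0.06, so λ = 200 × 0.06/0.6889 = 17.42 and power is 97.0%.

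**3. The two-step procedure.** This is the probability that the ANOVA rejects and the t-test for the pair differing by 0.3 also rejects, estimated from 400,000 simulated trials per setting.

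| n per group | third mean midway | third mean equal to one of the pair |
|---|---|---|
| 130 | 73.0% | 79.0% |
| 133 | 74.0% | 80.1% |
| 150 | 79.6% | 85.0% |
| 152 | 80.2% | 85.6% |
| 200 | 90.4% | 94.0% |

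The protocol's 80% is not reproduced at n = 200. It appears at about 150 per group in the least favourable case and about 133 in the other.

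**4. Difference detectable with 80% power at n = 200.** With the third mean midway, d = 0.26 gives two-step power of 79.7%. As a reduction, 1 − exp(-0.26) = 22.9%. With the third mean equal to one of the pair, 0.26 has about 85% power.

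**5. Could another reading give 80% at n = 200?**
- Effect taken as exactly 25%, ln(0.75) = −0.288: two-step power 87.7% to 91.9%.
- Bonferroni over three pairs: 88.9% for the t-test. This contradicts the stated 5% per test.
- t-test at 1%: 85.1%.
- One-sided t-test: 97.6%.
- Four-group ANOVA step, least favourable: 87.1%.
- Larger SD: about 0.95 would be needed with the third mean midway (two-step power 80.4%), against the stated 0.83.
- Bonferroni over the six pairs of four groups, with effect 0.288: 79.6%. This matches, but contradicts both the three groups and the 5% per test.
- A 25% loss, leaving 150 evaluable: 79.6% in the least favourable case. This also matches, but no loss is stated.

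**The case against.** The arithmetic is not in dispute; the objections concern its weight and wording.

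- **The error is conservative.** Power is understated, so no participant number, test or decision rule has to change. This stands, and it limits the seriousness of the point.
- **The study is a pilot and its size is presented as chosen.** Section 10.1 cites limited prior data, fixes 400 per group, and then reports what 200 can detect. It does not say that 200 was derived from an 80% target. That is fair, but the reported power is still a definite figure tied to those inputs.
- **The figure of 150 is a worst case.** Section 12 expects both *M. perstans* and *O. volvulus* infection to improve insulin sensitivity, which is closer to the case where the third mean equals one of the pair. About 133 per group then suffices. This stands, so the number needed should be given as a range or with its assumption.
- **A 25% loss allowance may lie behind the 80%.** It fits the least favourable case almost exactly, so an omitted assumption is a real possibility. The section nevertheless attaches 80% to 200 cases per group. If a loss was assumed, leaving it out is the fault, and the remedy is still one sentence.
- **A null result is read from its estimate and confidence interval, not from planned power.** This is correct. The case for correcting the figure rests on judging losses and clustering, not on interpreting a null result.

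**Conclusion.** The point holds: the sentence is wrong as written. On the protocol's own inputs, the two-step procedure at 200 per group has power of about 90% (third mean midway) to 94% (third mean equal to one of the pair), against the stated 80%. That understates power by 10 to 14 percentage points.

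The undeclared margin is 200 against about 150, which is a 25% loss or a design effect of 200/150 = 1.33. If the third mean equals one of the pair, it is 200 against about 133, a loss of about 34%.

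These figures assume natural logs, normal values with a common SD of 0.83, independent participants, 200 evaluable per group, and a between-group comparison of one log(HOMA-IR) value per person. Clustering by village or a larger true SD would use up some of the margin. This is a correction that should be made, but it does not threaten the design.

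**What to change.** Replace the power sentence in section 10.1 with one of the following, according to what was intended.

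- *With 200 evaluable participants per obese group and SD 0.83, the two-step procedure has at least about 90% power to detect a difference of 0.3 in mean log(HOMA-IR) between two groups, whatever the third group's mean (80% power for a difference of about 0.26 when the third mean lies midway).*
- *Power of 80% for a difference of 0.3 requires about 150 evaluable participants per obese group in the least favourable case; 200 are planned, which allows for a 25% loss or a design effect of about 1.3.*

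If the number of groups in the primary test changes, the figure should be recomputed for that test. The cost is one sentence, with no change to enrolment or to the analysis.
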